### 2.8. Data management and quality control

Data will be collected throughout the study and recorded in a case report form Any modification of the study protocol will be requested in advance and reviewed and approved by the ethics committee of our hospital. All data will be stored in an independent storage room to ensure data confidentiality and reliability. A Data and Safety Monitoring Board will be established. The members of the Data and Safety Monitoring Board include physicians, trial-methods experts, clinical pharmacists, statisticians, and members of the ethics committee. They will perform risk assessment and safety analysis procedures according to termination conditions. Access to the database will be restricted to researchers on this research team. The information of the subjects will not be disclosed and shared without the written permission of the subjects.

### 2.9. Statistical analysis

We will use excel to establish a database, and the outcome data will be statistically analyzed by the full analysis set and per-protocol set. Safety evaluation data will be based on the safety set. The statistical evaluation of full analysis set will follow the intention-to-treat principle. In this study, SPSS21.0 (IBM Company, New York, NY) software will be used for data analysis. The count data will be described by frequency percentage (n (%)) and a Chi-squared test will be used. Measurement data will be described by mean ± standard deviation ($\bar{x}$ ±s) or interquartile range M (P25, P75). One-way analysis of variance will be used for normal distribution comparison between groups, paired sample *t* test will be used for intra-group comparison, and Wilcoxon rank sum test will be used for skewed distribution. *P* < .05 is considered statistically significant.

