#### 2.3..2. Inclusion criteria.

(1) Meet the diagnostic criteria of type 2 DKD;(2) Age ≥ 18 years old and ≤ 70 years old, regardless of gender;(3) With the 24-hour urinary protein quantification was 0.5 to 3.5 g;(4) With serum creatinine < 265μmol/L (3 mg/dL);(5) Patients voluntarily participated in the trial and signed informed consent.

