### 2.4. Sample size

The sample size of this study was calculated based on the change in 24-hour urinary protein quantification (the difference in the standard deviation of the mean value of 24-hour urinary protein quantification before and after treatment) after 12 weeks of treatment, which was 0.87 ± 0.41 in the treatment group according to the results of the pilot study, and the control group was 0.65 ± 0.33. PASS15.0 software was used to estimate the sample size and set α = 0.05, β = 0.10. Finally, 37 participants are needed in each group, and the dropout rate was estimated to be 10%. The total required sample size will be 84 cases, 42 cases in each group.

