### 2.7. Outcome indicators

#### 2.7..1. Primary outcome indicator.

24-hour urinary protein quantification, which will be measured at baseline, weeks 8 and 12 of treatment, and weeks 12 and 24 of follow-up.

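### The between-group test has no baseline covariate, and the plan does not say whether 24-hour urinary protein level or change is tested; ANCOVA on baseline would be more precise at no extra data cost

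*Protocol article*

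**What the plan says.** Section 2.9 (Statistical analysis) fixes the tests. For normally distributed measurements, "One-way analysis of variance will be used for normal distribution comparison between groups". Skewed measurements go to a Wilcoxon rank sum test. Within each group, "paired sample *t* test will be used for intra-group comparison". No covariate is named, and neither the analysed quantity (level or change) nor the visit is given.

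Section 2.7.1 defines the primary outcome as "24-hour urinary protein quantification, which will be measured at baseline, weeks 8 and 12 of treatment, and weeks 12 and 24 of follow-up". That is a measurement and its schedule, with no change score and no primary visit.

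Section 2.4 (Sample size) states: "The sample size of this study was calculated based on the change in 24-hour urinary protein quantification" over 12 weeks of treatment. The pilot value "which was 0.87 ± 0.41 in the treatment group according to the results of the pilot study" is set against 0.65 ± 0.33 in the control group.

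Section 2.3.2 admits patients over a wide range of the same variable: "With the 24-hour urinary protein quantification was 0.5 to 3.5 g".

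**The concern.** With two groups, a one-way ANOVA is an unadjusted two-sample t test. The primary variable is measured at baseline in every patient, and its eligibility window spans a factor of seven (3.5/0.5). The one test in section 2.9 that necessarily uses baseline is the within-group paired test, which does not estimate the treatment effect.

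Two things are at stake. The first is precision: baseline usually predicts the later value, and an analysis that does not model it leaves explainable variance in the error term. The second is chance imbalance. With about 40 patients per group, baseline means can differ by an amount that matters next to the planned effect. A comparison of levels leaves that difference in the estimate, and a comparison of changes overcorrects it through regression to the mean.

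Because section 2.9 does not settle level or change, the choice could also be made after the data are seen. The article itself names the test, so this is a stated method that can be improved and not detail left to an unseen analysis plan.

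**Working it through.** **Inputs from section 2.4.** Mean changes 0.87 (SD 0.41) and 0.65 (SD 0.33); α = 0.05; β = 0.10; 37 per group before dropout, 42 after.

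- Difference: 0.87 − 0.65 = 0.22.
- Pooled SD of change: √((0.41² + 0.33²)/2) = √0.1385 = 0.372.

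**The plan's own figure.** For a two-sided test with 90% power, n per group = 2 × (1.960 + 1.282)² × 0.1385/0.22² = 60.1, so 61 (62 with the t distribution). A one-sided test needs 50. The stated 37 is not reproduced. The dropout step is right: 37/0.9 = 41.1, so 42. Two-sided power for the change score with 37 per group is Φ(0.22/(0.372 × √(2/37)) − 1.96) = Φ(0.58) = 72% (71% with the t distribution). The drop from 90% to 72% is a sample-size matter and exists before any choice of analysis.

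**Comparing the three analyses.** Let σ be the SD of the level, taken as equal at baseline and week 12, and r the within-patient correlation. The documents do not give r, so a range is shown.

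- SD of change = σ√(2(1 − r)), held at 0.372. Hence σ = 0.372/√(2(1 − r)).
- SD for a comparison of levels = σ.
- Residual SD for ANCOVA = σ√(1 − r²).
- Power = Φ(0.22/(SD × √(2/37)) − 1.96).

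| r | SD level | SD change | SD ANCOVA | Power level | Power change | Power ANCOVA |
|---|---|---|---|---|---|---|
| 0.3 | 0.315 | 0.372 | 0.300 | 85% | 72% | 88% |
| 0.5 | 0.372 | 0.372 | 0.322 | 72% | 72% | 84% |
| 0.7 | 0.480 | 0.372 | 0.343 | 50% | 72% | 79% |
| 0.9 | 0.832 | 0.372 | 0.363 | 20% | 72% | 74% |

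ANCOVA has the smallest SD in every row. Its variance relative to the change score is (1 − r²)/(2(1 − r)) = (1 + r)/2, that is 0.75, 0.85 and 0.95 at r = 0.5, 0.7 and 0.9. The gain shrinks as r rises. The number per group needed for 90% power with ANCOVA is 40, 46, 52 and 58 for the four rows, always above 37.

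**Chance imbalance.** The standard error of the baseline difference between groups of 37 is σ√(2/37): 0.09 g at r = 0.5, 0.11 g at r = 0.7 and 0.19 g at r = 0.9, against a planned effect of 0.22 g. Under equal variances the slope on baseline is r. A baseline difference D therefore shifts the level comparison by rD and the comparison of final minus baseline by −(1 − r)D. With D equal to one standard error at r = 0.7 (0.112 g), the shifts are 0.7 × 0.112 = 0.08 g and −0.3 × 0.112 = −0.03 g. ANCOVA removes this shift.

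**The case against.** The strongest reply is that section 2.9 may mean exactly what section 2.4 sizes. The 12-week change is the only quantity the article specifies closely enough to analyse. A one-way ANOVA on that change is the two-sample t test, which uses baseline and matches the sizing. This stands. A reader might infer that the plan ignores baseline altogether, or that its test contradicts the sizing variable. The text shows neither; it shows only that the analysed quantity is left open and that no covariate is named.

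A reader might also infer that the stated test throws away most of the planned power. That does not follow. At r = 0.5 level and change do equally well, and at r = 0.3 the level does better (85% against 72%). Only at high r does the level lose heavily, and r is not in the documents. Very low figures for the level, near 20%, need a week-12 SD of about 0.83 to 0.87. One way to get there is to spread patients uniformly over the eligibility window (3.0/√12 = 0.87), but the documents give no SD for the level at any visit.

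Finally, the unadjusted test controls type I error under randomisation, and chance imbalance is not systematic bias. That is correct, and it limits the point to precision and to the estimate conditional on the baselines actually observed.

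**Conclusion.** The point holds as an improvement to a stated method, not as an error that would invalidate the result. Section 2.9 fixes an unadjusted between-group test and leaves level or change open. ANCOVA on baseline is at least as good as either at every correlation examined.

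Against a change-score test the gain is modest: about 12 points of power at r = 0.5, 7 at r = 0.7 and 2 at r = 0.9. Against the level it is about 3 points at r = 0.3 and 12 at r = 0.5, and becomes large above that (about 29 points at r = 0.7 and 54 at r = 0.9).

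These sizes rest on the pilot SDs, equal variances at the two visits, 37 analysed per group, a two-sided 0.05 test, the normal approximation and an assumed range for r. The fall from the stated 90% to 72% on the change score must not be charged to the analysis. It comes from the sample size, and ANCOVA does not restore 90% with 37 per group for r between 0.3 and 0.9 (74% to 88%).

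**What to change.** In section 2.9, state that the primary comparison is an ANCOVA of 24-hour urinary protein at week 12 of treatment, with group as factor and baseline 24-hour urinary protein as covariate. Report the adjusted difference with its 95% confidence interval. The dependent variable may be the week-12 value or the change from baseline: with baseline in the model, both give the same treatment estimate (apart from sign, if change is written as a reduction), so the question of level or change disappears. If the distribution is skewed, fit the same model to log-transformed values at both visits and report the back-transformed ratio.

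The cost is one sentence, passed through the ethics review that section 2.8 requires for protocol changes, and settled before outcome data are examined by group. No new measurement or visit is needed, and the model is standard in the named software. The sample size in section 2.4 has to be corrected separately.

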#### 2.3..4. Eliminating standard.

(1) Patients with severe adverse events and/or severe complications which will be not suitable for further trial;(2) Patients’ poor compliance affected the judgment of the results;(3) The patient’s condition progressed rapidly during the treatment and the treatment regimen needed to be changed;(4) The subject requested to withdraw from the trial for any reason.

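### Section 2.9 names unadjusted single-visit tests for a primary outcome measured at baseline and four later visits; unless missing values are handled elsewhere, this gives a complete-case comparison that fits poorly with intention-to-treat

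*Protocol article*

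**What the plan says.** Section 2.7.1 of the protocol article gives the primary outcome as "24-hour urinary protein quantification, which will be measured at baseline, weeks 8 and 12 of treatment, and weeks 12 and 24 of follow-up". Table 1 shows the same visits.

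For the comparison between groups, section 2.9 states "One-way analysis of variance will be used for normal distribution comparison between groups" and "Wilcoxon rank sum test will be used for skewed distribution". With two groups, the one-way ANOVA is a two-sample t test. No baseline covariate and no longitudinal model is named, and the section does not say whether the value or its change from baseline is tested.

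The same section says that "the outcome data will be statistically analyzed by the full analysis set and per-protocol set", and adds: "The statistical evaluation of full analysis set will follow the intention-to-treat principle".

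Section 2.4 sizes the trial on the change after 12 weeks of treatment and says "the dropout rate was estimated to be 10" per cent. Section 2.3.4 lists grounds for elimination. These include poor compliance, withdrawal, and the case where the patient's "condition progressed rapidly during the treatment and the treatment regimen needed to be changed". It does not say whether elimination means leaving treatment, follow-up or the analysis.

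**The concern.** A one-way ANOVA or rank sum test at week 12 takes one number per patient. A patient seen at week 8 but not at week 12 has nothing to contribute unless a value is imputed, although the week-8 result shows how that patient was doing. Baseline enters only by subtraction, and only if change is the variable tested.

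This would matter little if loss were unrelated to outcome. Two features make a relation plausible. Rapid progression is a listed ground for elimination, and proteinuria is itself a marker of progression. The arms also differ in burden: section 2.6 has one arm treated for 30 minutes every other day, section 2.7 has both arms measured at the same visits, and the discussion concedes that the trial could not be double blind. Loss could therefore depend on outcome and differ between arms. The stake is bias in the primary contrast, in either direction.

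**Working it through.** **The plan's own dropout step.** 37 / (1 − 0.10) = 41.1, rounded up to 42 per arm and 84 in total. This agrees with section 2.4. At 10% loss, 42 × 0.90 = 37.8, so about 38 per arm have a week-12 value and about 8 of 84 patients do not. (The 37 does not itself follow from the stated α, β, means and SDs. That is a separate matter and is not used below.)

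**Inputs from section 2.4.** Change at week 12: 0.87 (SD 0.41) in the treatment group and 0.65 (SD 0.33) in the control group. Planned difference: 0.87 − 0.65 = 0.22. I read these as grams of reduction, so that a small change is a poor result.

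**Assumptions, not in the protocol.** Changes are normally distributed. The correlation ρ between week-8 and week-12 change is 0.5 to 0.8. Loss rates by arm are as shown below.

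**Worst case: exactly the poorest week-8 responders leave.** If a share q of an arm leaves this way, the completers' week-12 mean is too high by ρ × SD × h(q), where h(q) = φ(z_q) / (1 − q).

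- h(0.05) = 0.1031 / 0.95 = 0.1086
- h(0.10) = 0.1755 / 0.90 = 0.1950
- h(0.15) = 0.2332 / 0.85 = 0.2743

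Bias in the group difference = ρ × [0.41 × h(q_T) − 0.33 × h(q_C)].

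| Loss, treatment / control | Bracket | Bias, ρ 0.5 to 0.8 | Share of 0.22 |
|---|---|---|---|
| 10% / 10% | 0.1950 × 0.08 = 0.0156 | +0.008 to +0.012 g | about 4% to 6% |
| 5% / 15% | 0.04453 − 0.09052 = −0.0460 | −0.023 to −0.037 g | 10% to 17% |
| 15% / 5% | 0.11246 − 0.03584 = +0.0766 | +0.038 to +0.061 g | 17% to 28% |

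Simulation with 42 per arm agrees: +0.008 to +0.014 g, −0.021 to −0.035 g and +0.037 to +0.057 g in the same order. A simpler calculation, with dropouts 0.5 to 1 SD worse than completers, gives 0.004 to 0.008 g for equal 10% loss and 0.022 to 0.045 g for 15% / 5%.

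**Partial dependence.** If leaving depends on the week-8 z-score plus noise of SD 1.5, the unequal-loss biases fall to about −0.01 to −0.02 g and +0.02 to +0.03 g, roughly half.

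**What a likelihood-based analysis using week 8 recovers.**

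- Loss driven by week 8 only: bias of at most about 0.002 g. This follows by construction, since the cause of loss is observed.
- Loss driven by the unseen week-12 value: −0.022 to −0.037 g (5% / 15%) and +0.036 to +0.059 g (15% / 5%) remain.
- Loss driven by worsening between weeks 8 and 12: the model can do worse than complete cases. At ρ 0.7 and 15% / 5%, its bias is +0.052 g against +0.030 g.

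The standard error of the difference is about 0.084 g and almost the same under both analyses, so using week 8 adds little precision.

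**The case against.** A reader might infer that the plan excludes anyone who misses a visit and so abandons intention-to-treat. The document does not say that. ANOVA and rank sum tests are not missing-data rules, and imputation followed by ANOVA would keep everyone. Such a rule may sit in the full protocol or the SAP, neither of which is shown, and its absence from a journal article is no fault. This stands: complete-case analysis is the likely default of the named tests, not a stated fact.

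A reader might also infer that a single-visit test is invalid because the outcome is repeated. It is not. Two randomised groups may be compared at week 12, the time point used for sizing, and with complete data the test is sound.

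Nor does the protocol support the larger bias figures as a forecast. It gives one 10% dropout rate and no split by arm. It also gives no ground for claiming that a mixed model would cure the problem. Progression before week 8 leaves no post-baseline value, and worsening after week 8 may go unobserved.

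What survives is that section 2.9 does name a method. That method makes no adjustment for baseline and no use of week 8, and the text does not reconcile the elimination list with intention-to-treat. This is a weak choice that the text fixes, not merely a missing detail.

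**Conclusion.** The point holds in limited form. The named tests are a poor match for a primary outcome with a baseline and four later values. Unless missing values are handled elsewhere, they do not by themselves deliver the stated principle.

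At the plan's own 10% loss, if equal in both arms, the bias is about 0.01 g (3% to 7% of 0.22 g), small beside a standard error of about 0.084 g. It becomes material, about 0.02 to 0.06 g (10% to 28%), only if loss differs threefold between arms and strictly the worst week-8 patients leave. With a looser link to week 8 it is roughly half that. The correlation, the loss by arm and the dropout mechanism are all assumptions. The change is worth making because it is cheap and uses data already scheduled, not because serious bias has been shown.

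**What to change.** In section 2.9, make the primary analysis of 24-hour urinary protein a linear mixed model for repeated measures in the full analysis set. Include group, visit, group-by-visit and baseline 24-hour protein, with all post-baseline visits and an unstructured covariance, on log values if the data are skewed. Take the group contrast at week 12 of treatment as primary, which matches the sizing in section 2.4. Keep the ANOVA or rank sum test as a sensitivity analysis.

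State that patients who meet a ground in section 2.3.4 stay in the full analysis set with all their collected values, so that sections 2.3.4 and 2.9 agree. Changing the model alone does not settle this.

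The cost is a few lines of text and a slightly more complex analysis, with no extra visits or patients. The limit should be stated: the model removes bias only where dropout is explained by observed values. It does not help with patients lost before week 8 or lost because of unobserved worsening.

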## 3. Discussion

DKD is a serious microvascular complication, which is caused by long-term diabetes or poor blood glucose control, and is also an important factor in the death of diabetic patients.^[19]^ The pathogenesis of DKD is complex, and the early symptoms are occult. Therefore, clinical attention should be paid to the treatment and control of DKD.^[20]^

The pathogenesis of DKD is complicated. In recent years, the theory of autophagy has been widely used in the study of metabolic diseases, and it has been found that it is closely related to the damage of target organs. Autophagy is an important life phenomenon of living organisms; however, if autophagy is abnormally activated due to environmental stress and other factors, its autophagy expression beyond a certain physiological range will in turn cause damage to target cells, thus causing damage to target organs. The occurrence of diabetic kidney damage is closely related to the abnormal activity of autophagy and directly related to the degree of urinary protein.^[15]^ Western medicine treatment is mainly aimed to control the risk factors and further control the progress of the disease, but the clinical efficacy is still not satisfied.^[21]^

Studies have confirmed that the bidirectional regulation of acupuncture and moxibustion has something in common with the bidirectional regulation of autophagy expression. Acupuncture and moxibustion can effectively reduce urinary microprotein excretion, alleviate kidney injury and improve renal function in patients with early DKD.^[21,22]^ Warm acupuncture is a further development of acupuncture, clinical studies have shown which can reduce blood viscosity, improve microcirculation, regulate immune function, and inhibit platelet aggregation.^[23]^ Although evidence has shown that warm acupuncture is beneficial for patients with DKD, whether it can be used as a complementary or alternative treatment regimen for DKD remains controversial. We will use this study to investigate the clinical efficacy of warm acupuncture in the treatment of DKD, which is beneficial for both patients and clinical decision makers.

There are also some shortcomings in this study: due to the factors of treatment methods, this study could not achieve double blindness, which may have some impact on the study results; at the same time, there may be population regionalization in the study.
